### Safety variables

The primary safety outcomes of interest are rates of adverse events (AEs) in treated patients, with identified risks being anti-velmanase alfa-immunoglobulin G antibody (anti-drug antibody; ADA), infusion-related reactions, and hypersensitivity (Table 1). In all patients, treated and untreated, secondary safety outcomes and other data related to disease progression or AEs related to other drugs will be included: the evaluation of medical events (including but not limited to acute renal failure and loss of consciousness), change in vital signs (including systolic and diastolic blood pressure), laboratory tests (hematology and chemistry), physical examination, and electrocardiogram results. The suggested schedule of assessments is shown in Table 2, but assessments will be made based on the participating centers’ Standard Operating Procedures.

**Table 1 Tab1:** Effectiveness and safety outcomes

Effectiveness outcomes	Safety outcomes
Laboratory assessments: • Serum oligosaccharides (µmol/L) • Serum IgG, IgA, and IgM Functional assessments: • 3MSCT (steps/min) • 6MWT (m)^a^ • 2MWT (m)^a^ • FVC (L and % of predicted)^a^ Health Assessment Questionnaires: • EQ-5D-5L • Zarit Burden Interview • QoL questionnaire • Behavior checklists for child and adult Other: • Psychotic events (rate)	• AEs: serious and nonserious • ADRs: including serious and nonserious • AEs leading to treatment discontinuation and death • Any identified risks including anti-VA-IgG antibody, infusion-related reactions, and hypersensitivity • Any potential risk of acute renal failure, loss of consciousness, and medication errors • Vital signs: SBP, DBP, and pulse rate • Electrocardiogram • Laboratory tests (hematology and chemistry) • Physical examination

*2MWT* 2-min walk test, *3MSCT* 3-min stair-climb test, *6MWT* 6-minwalk test, *ADR* adverse drug reaction, *AE* adverse event, *DBP* diastolic blood pressure, *FVC* forced vital capacity, *FVC%* forced vital capacity, percent of predicted, *Ig* immunoglobulin, *QoL* quality of life, *SBP* systolic blood pressure, *VA* velmanase alfa

^a^In patients < 4 years of age, 3MSCT, 2MWT, and FVC% of predicted will be proposed based on physician judgment

**Table 2 Tab2:** Suggested schedule

Procedure	Registry inclusion visit (~ –7 days)	Registry baseline visit (time 0)	Unscheduled follow-up routine clinical visit^a^	Six-month follow-up routine clinical visits^b^	Yearly follow-up routine clinical visits
*Administrative*					
Informed consent form	X	X^c^			
Inclusion/exclusion criteria	X	X^c^			
Medical and disease history (including disease onset, residual enzymatic activity, genotype mutations, bone marrow transplantation) and concomitant illnesses	X	X^c,d^			
Previous and concomitant medications, including VA in hospital or home infusion setting		X^d^	X	X	X
Concomitant procedures	X	X	X	X	X
Physical examination^e^ (vital signs and anthropometric measurements, including rate of growth)		X	X	X	X
Demographics	X	X^c^			
*Administration of medication*					
VA therapy, in hospital or home infusion setting^f^		X	X	X	X
*Assessments*^g^					
Standard hematological tests^h^		X	X		X
Laboratory chemistry^i^		X	X		X
Anti-VA-IgG antibody (ADA)^j^		X	X		X
Oligosaccharides in serum^j^		X	X		X
Serum IgG, IgA, IgM^j^		X	X		X
3MSCT, when applicable^k^		X			X
6MWT, when applicable^k^		X			X
2MWT, when applicable^l^		X			X
FVC (L and % of predicted)		X	X		X
Electrocardiogram		X	X		X
Hearing test (PTA)		X	X		
Psychotic events		X	X		X
AEs/ADRs^m^	X	X	X	X	X
*Health Assessment Questionnaires*					
EQ-5D-5L		X			X
Zarit Burden Interview		X			X
CHAQ		X			X
Behavior checklists^n^		X			X

*3MSCT*3-min stair climbing test, *2MWT*2-min walk test, *6MWT*6-min walk test, *ABCL* Adult Behavior Checklist, *AE* adverse event, *ADA* alfa-immunoglobulin G antibody, *ADR* adverse drug reaction, *ALP* alkaline phosphatase, *ALT* alanine aminotransferase, *ASR* Adult Self-Report, *AST* aspartate transaminase, *CBCL* Child Behavior Checklist, *CHAQ* Childhood Health Assessment Questionnaire, *FVC* forced vital capacity, *Ig* immunoglobulin, *L* liter, *LDH* lactate dehydrogenase, *OABCL* Older Adult Behavior Checklist, *PTA* pure tone audiometry, *RMP* risk management plan, *VA* velmanase alfa

Actual assessments performed per participating center Standard Operating Procedures

^a^Unscheduled follow-up visits can be performed at, but not limited to, 3 months after VA treatment start, or whenever deemed appropriate according to treating physician’s judgment for patients who start VA treatment within 1 year prior to Registry inclusion

^b^Additional follow-up visit after 6 months is highly recommended for patients who start VA treatment within 1 year prior to registry inclusion

^c^If not taken or collected at registry inclusion visit

^d^Patients’ retrospective data may be collected at the time of registry enrolment if available. Baseline visits are recommended to be repeated for those patients who will start VA therapy during the course of the study, before therapy is initiated

^e^Physical examination to collect vital signs, anthropometric measurements like height, weight, rate of growth, and the ability to perform the endurance test at the study visit

^f^If applicable, information regarding weekly VA therapy received by the patient need to be recorded within all the registry duration

^g^All assessments mentioned in the above table will be collected only if considered necessary and available as part of routine clinical practice by the treating physician; no additional tests specific to the registry will be done

^h^Standard test for hematology assessed by local laboratory if available per clinical practice of the site: hemoglobin, hematocrit, platelet count, red blood cells, and white blood cells with differential count (all expressed in %, as well as in absolute numbers)

^i^Standard test for hematology assessed by local laboratory if available per clinical practice: serum electrolytes, creatinine, creatine-kinase, amylase, AST, ALT, ALP, albumin, bilirubin (total and direct), LDH

^j^The markers (oligosaccharides in serum, IgG, IgA, and ADA) will be evaluated through a central laboratory in European countries other than Germany. In Germany, marker testing will take place according to local routine clinical practice

^k^In patients 4 years and older, and when applicable according to the judgment of treating physician

^l^In patients under 4 years of age and when applicable according to the judgment of treating physician

^m^AEs/ADRs based on all risk categories associated with VA European RMP, including infusion-related reactions and hypersensitivity (as identified risks), acute renal failure, loss of consciousness and medication errors (as potential risks). Data on pregnancy (including birth and newborn data) and lactation (as missing information) will be also collected if available

^n^One of the behavior checklists (CBCL pre-scholar/scholar, ABCL/ASR [self-reporting], OABCL) will be used to the applicable age and according to the judgment of treating physician

### Effectiveness variables

Efficacy outcomes to be assessed during routine clinical care are shown in Table 1. For patients under 4 years of age, a 3-min stair climb test (3MSCT) and 2-min walk test (2MWT) are suggested. The forced vital capacity (% volume predicted) is suggested for patients over 4 years of age, and according to the judgment of the treating physician. The proposed schedule of assessments is shown in Table 2, but, again, assessments will be made based on the participating centers’ Standard Operating Procedures.

A global treatment response (GTR) to velmanase alfa will be evaluated in velmanase alfa-naïve patients able to perform the functional tests after 3 years of treatment. The GTR will assess patients in three clinical domains (pharmacodynamic, functional, and QoL) consisting of 1 or > 1 endpoint (Table 3). The pharmacodynamic domain comprises a measure of the accumulated substrate in alpha-mannosidase deficiency, the main pathogenic factor for disease manifestations; a decrease in oligosaccharides is a key biomarker of the pharmacologic effect of the ERT [4]. The second domain includes pulmonary function, endurance, and fine and gross motor proficiency, i.e., all the functional endpoints of the disease [4]. The QoL domain relates to patient-related outcomes of disease burden, disability, and pain [4]. A global response is defined as improvements exceeding the established minimal clinical important difference (MCID) (Table 3) in ≥ 1 endpoint in ≥ 2 of the domains [4]. The MCIDs are derived on the basis of those used in clinical conditions with the highest similarity to alpha-mannosidosis (proxy diseases) [14–17]. Collection of the same effectiveness variables is suggested for patients who are not treated with velmanase alfa, in order to support the description of the natural course of the disease.

**Table 3 Tab3:** Clinical domains, endpoints, and MCID thresholds for the GTR

Domain	Endpoint	Established MCID^a^
Pharmacodynamic	Serum oligosaccharides	Last serum oligosaccharide value ≤ 4 µmol/L
Functional	3MSCT	Improvement ≥ 7 steps/min [14]
	6MWT	Improvement ≥ 30 m [16]
	FVC%	Improvement ≥ 10% [15]
Quality of life	CHAQ DI	Improvement ≤ –0.130 [17]
	CHAQ Pain VAS	Improvement ≤ –0.246 [17]

*3MSCT* 3-min stair-climb test, *6MWT* 6-min walk test, *CHAQ DI* Child Health Assessment Questionnaire Disability Index, *CHAQ Pain VAS* Child Health Assessment Questionnaire Pain Visual Analog Scale, *FVC%* forced volume capacity, percentage of predicted, *GTR* Global Treatment Response, *MCID* minimal clinically important difference, *MPS IV A* mucopolysaccharidosis type IV A

^a^MCID were derived from proxy diseases (3MSCT from MPS IV A clinical trials; 6MWT and FVC% from Pompe; CHAQ DI and CHAQ Pain VAS from juvenile arthritis)

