## Methods

### Study design

SPARKLE is a post-authorization safety and efficacy registry in Europe, designed as a multicenter, international, prospective cohort study of patients with alpha-mannosidosis (Fig. 1). The primary objective is to assess the long-term effectiveness and safety of treatment with velmanase alfa under conditions of routine clinical care; secondary objectives include expanding the current understanding of alpha-mannosidosis by collecting data to characterize the natural history of the disease. Source data will be collected by the investigator in the patient file and captured in an electronic case report form (eCRF). This also includes data from patients receiving treatment in a home-care setting. The study, which started patient enrollment in 2020, has an indefinite recruitment period. Patients will be followed for up to 15 years after inclusion. The end of the study is defined as the last visit of the last patient registered in the study. The study will be conducted under conditions of routine clinical practice, according to the treating physician, without mandatory registry assessments. Patients are eligible for the study irrespective of treatment (velmanase alfa, hematopoietic stem cell transplantation or any biologic substance received as part of a clinical trial during participation in the registry).

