### Study size

As this is an observational study and there is no formal hypothesis testing, the size of the study was conceptualized based on assumed different proportions of GTR in treatment-naïve patients who can perform functional tests after 3 years of treatment. Assuming at least 70 treated patients are enrolled, and assuming a GTR of at least 0.60, the lower limit of the two-sided 95% confidence interval (Clopper–Pearson) is always above 45.0% (Table 4), which is considered a clinically relevant response. Thus, the efficacy analysis is based on a hypothetical treated population of at least 70 patients.

**Table 4 Tab4:** Efficacy analysis based on hypothetical treated population of at least 70 patients

Expected proportion	95% CI lower limit	95% CI upper limit	95% actual width
0.60	0.476	0.715	0.239
0.65	0.527	0.760	0.234
0.70	0.579	0.804	0.225
0.75	0.632	0.846	0.214
0.80	0.687	0.886	0.199

*CI* confidence interval

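### The global response is attributed to velmanase alfa, yet its population does not consistently exclude or separate patients with a transplant or trial biologic, so the drug may be credited with their effects

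*Protocol article*

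**What the plan says.** - **Effectiveness variables:** "A global treatment response (GTR) to velmanase alfa will be evaluated in velmanase alfa-naïve patients able to perform the functional tests", with assessment at three years. Response requires at least one endpoint past its threshold in at least two of three domains. Table 3 sets the pharmacodynamic threshold as an absolute last serum oligosaccharide value of at most 4 µmol/L. All functional and CHAQ thresholds are improvements.
- **Study design:** "Patients are eligible for the study irrespective of treatment (velmanase alfa, hematopoietic stem cell transplantation or any biologic substance". The biologic meant is one given within a trial while the patient is in the registry. **Patient population** states no exclusion criteria for patients with the disease.
- **Patient population:** the velmanase alfa safety and efficacy sets are defined by exposure to the drug, follow-up and available evaluations. The windows of 1 and 12 months refer to velmanase alfa only.
- **Statistical analyses:** the covariates for the regression and the propensity score are age, sex, sibships, genotype, residual enzyme activity and CHAQ Disability Index. No other treatment is listed.
- **Table 2:** records "Previous and concomitant medications, including VA in hospital or home infusion setting", concomitant procedures, and bone marrow transplantation within the medical history.
- **Study size:** describes the GTR population as treatment-naïve, without tying this to velmanase alfa. For a minimum of 70 treated patients and a response rate of 0.60 or more, it concludes that "the lower limit of the two-sided 95% confidence interval (Clopper–Pearson) is always above 45.0" per cent, a level it regards as clinically relevant.

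**The concern.** The GTR is a single-group rate labelled as a response to one drug. That label needs a population, or an analysis, in which another disease-directed treatment cannot supply the response. The article names two such treatments as permitted and collects them, but neither the analysis sets nor the covariates use that information. The two descriptions of the GTR population also disagree: a patient transplanted before velmanase alfa is included under Effectiveness variables and arguably excluded under Study size. Neither description deals with a transplant or trial biologic that starts during the three years.

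At stake is the meaning of the primary effectiveness rate in a post-authorization commitment, and of its comparison with 45%. In a single-group rate, a helpful second treatment can only push the result upward.

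**Working it through.** **Step 1. How another treatment can enter the GTR.** Baseline and demographic variables takes baseline for treated patients at the start of velmanase alfa. The article gives no effect size for transplant or a trial biologic, so that either can lower oligosaccharides or improve function is an assumption here.

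- *Transplant before velmanase alfa, patient stable:* functional and CHAQ criteria require change after baseline, so the transplant does not by itself meet them. The oligosaccharide criterion is a last value, so a patient already at or below 4 µmol/L meets that domain with no change on the drug. One further improvement, for example a CHAQ Disability Index change of –0.130, makes a global responder.
- *Transplant or trial biologic started within the three years:* its gains fall after baseline and can count in all three domains.

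**Step 2. Reproduce the plan's figure.** Clopper–Pearson limits for x responders of n:

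- lower = 0.025 quantile of Beta(x, n − x + 1)
- upper = 0.975 quantile of Beta(x + 1, n − x)

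With n = 70 and x = 0.60 × 70 = 42, the limits are 0.476 and 0.715, width 0.239, as in Table 4. The other four rows also reproduce (0.65 and 0.75 with the non-integer x of 45.5 and 52.5). The plan's arithmetic is correct; the issue is attribution.

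**Step 3. Weight of one patient.** 1/70 = 1.4 percentage points.

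**Step 4. Sensitivity of the lower limit.** The number of affected patients is not given, so k (responders who owe their response to another treatment) is assumed.

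| Planned rate | Handling of the k responders | k | Result | Lower limit | Above 0.45? |
|---|---|---|---|---|---|
| 0.60 | non-response | 1 | 41/70 | 0.462 | yes |
| 0.60 | non-response | 2 | 40/70 | 0.447 | no |
| 0.60 | non-response | 5 | 37/70 | 0.406 | no |
| 0.60 | excluded | 3 | 39/67 | 0.455 | yes |
| 0.60 | excluded | 4 | 38/66 | 0.448 | no |
| 0.70 | non-response | 7 | 42/70 | 0.476 | yes |
| 0.70 | non-response | 10 | 39/70 | 0.433 | no |
| 0.80 | non-response | 10 | 46/70 | 0.534 | yes |

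**Step 5. Net shift in the rate.** Suppose 3 to 7 of 70 patients are co-treated (assumed) and all respond.

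- Ceiling, if none would have responded otherwise: 3/70 = 4.3 to 7/70 = 10 points.
- If they would otherwise respond at 0.60: 3/70 × 0.40 = 1.7 to 7/70 × 0.40 = 4.0 points.
- If they would otherwise respond at 0.80: 3/70 × 0.20 = 0.9 to 7/70 × 0.20 = 2.0 points.

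On the middle assumption, two surplus responders correspond to about five co-treated patients (5 × 0.40 = 2).

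**The case against.** The strongest reply is that this is a condensed article. Handling of treatment started during follow-up usually belongs in the analysis plan, which is not shown, and Study size may already exclude earlier transplants. The stated aim is effectiveness in routine care without formal hypothesis testing, so keeping co-treated patients is a legitimate summary. A stable earlier transplant cannot make a responder alone, and scoring every co-treated patient as a non-responder could bias the rate downward.

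Much of this stands. Silence about later treatment is not in itself an error, a routine-care rate is a valid quantity, and forced non-response is debatable as the primary rule. What does not fall away is what the article fixes: sets defined by velmanase alfa exposure, a covariate list without other treatment, a rate described as a response to the drug, and two descriptions of its population that disagree.

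Two stronger readings are tempting and are not supported:

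- A reader might infer that velmanase alfa is in fact credited with gains from other treatments. The article does not say how many treated patients have had one, or how large the effect is. Only a possibility of misattribution follows.
- A reader might infer that immunoglobulin replacement distorts the results, because serum IgG is an effectiveness outcome in Table 1. Such replacement appears nowhere in the document, and IgG is not a GTR endpoint in Table 3, so it cannot alter the GTR.

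**Conclusion.** The point holds in a limited form. As written, the GTR may include responses due wholly or partly to a transplant or trial biologic, and the article's two descriptions of the population do not settle whether earlier transplants are in or out. For earlier transplants the exposure is confined to the absolute oligosaccharide criterion; for treatment begun within the three years it extends to every domain.

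The size is unknown. If 3 to 7 of 70 patients were affected, a shift of about 2 to 4 points is more realistic than the 4 to 10 point ceiling. The comparison with 45% is fragile only near the lowest planned rate, where two reclassified responders are enough, and is robust at 0.70 and above unless many patients are affected. These figures assume that the other treatment helps and that co-treated patients respond.

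Upward bias is clear only for the single-group rate. The untreated set admits the same other treatments, so the direction in the treated-versus-untreated comparison is not fixed.

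**What to change.** 1. Reconcile Effectiveness variables and Study size with one definition: the headline GTR covers patients with no earlier transplant or other disease-directed biologic before velmanase alfa.
2. Report previously transplanted patients as a separate stratum outside the headline rate.
3. Add a GTR sensitivity analysis that excludes patients who start a transplant or such a biologic before year 3, or scores them as non-responders. State which in advance, and show the number of patients concerned.

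The cost is wording. Table 2 already records transplant history, medications and procedures, though as a suggested schedule, so completeness will depend on the sites. The downside is a slightly smaller headline group or a slightly lower rate.

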**Results:**

The SPARKLE registry is designed as a multicenter, multinational, noninterventional, prospective cohort study of patients with alpha-mannosidosis, starting patient enrollment in 2020. Patients will be followed for up to 15 years. Safety and effectiveness as post-authorization outcomes under routine clinical care in patients with treatment will be evaluated. The primary safety outcomes are the rate of adverse events (anti-velmanase alfa-immunoglobulin G antibody development, infusion-related reactions, and hypersensitivity). Secondary safety outcomes include the evaluation of medical events, change in vital signs, laboratory tests, physical examination, and electrocardiogram results. The primary effectiveness outcome is a global treatment response rate, evaluated as the individual aggregate of single endpoints from pharmacodynamic, functional, and quality-of-life effectiveness outcomes; secondary effectiveness outcomes are to characterize the population of patients with alpha-mannosidosis with regard to clinical manifestation, progression, and natural history of the disease. Any patient in the European Union with a diagnosis of alpha-mannosidosis who is willing to participate will likely be eligible for inclusion in the registry. Publications to disseminate scientific insights from the registry are planned.

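### The primary GTR population is worded so that it selects on status after 3 years of treatment, and early failures can then leave the denominator

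*Protocol article*

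**What the plan says.** The Abstract states: "The primary effectiveness outcome is a global treatment response rate". Under Effectiveness variables, GTR is to be evaluated in velmanase alfa-naïve "patients able to perform the functional tests after 3 years of treatment". A patient responds by exceeding the threshold "in ≥ 1 endpoint in ≥ 2 of the domains", the three domains being pharmacodynamic, functional and quality of life. Table 3 lists the stair-climb test, the 6-minute walk and FVC% in the functional domain.

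The Study size section plans on "proportions of GTR in treatment-naïve patients who can perform functional tests after 3 years of treatment". Its inputs are 70 or more enrolled treated patients and a response proportion of 0.60 or higher. Its conclusion is that "the lower limit of the two-sided 95% confidence interval (Clopper–Pearson) is always above 45.0" per cent, a level it calls clinically relevant. It also says that there is no formal hypothesis test.

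Three other places bear on the point:
- Patient population defines a wider velmanase alfa efficacy set, which keeps evaluations made on treatment and for 12 months after it.
- Baseline and demographic variables, and the physical-examination footnote to Table 2, record the ability to do the endurance test at baseline and at study visits.
- Table 1 lists "AEs leading to treatment discontinuation and death" among the safety outcomes, and Data management requires the main reason for withdrawal.

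**The concern.** In both places where the GTR population is given, the time qualifier directly follows the ability to do the tests. Taken that way, a patient enters the denominator only by still being on treatment and able to be tested at year 3. A patient who stopped for a reaction, died or lost the ability to do the tests would be left out, although such outcomes would often be regarded as treatment failures.

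The registry's primary objective is effectiveness under routine care. A rate among patients who remained treated and testable answers a narrower question, and it will usually look better. A planned comparison with untreated patients at 3 years, if it goes ahead, would inherit the same selection.

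This is not a complaint that a missing-data rule is absent, which an article may leave to the full protocol or SAP. The population itself is stated, twice, in wording that permits selection on a post-baseline status.

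**Working it through.** **1. The plan's own figures.** Inputs from Study size and Table 4: n = 70, proportions 0.60 to 0.80, two-sided 95% Clopper–Pearson. Lower limit = 0.025 quantile of Beta(x, n − x + 1). Upper limit = 0.975 quantile of Beta(x + 1, n − x). With x = 0.60 × 70 = 42 this gives 0.476 to 0.715, as printed. All 15 entries of Table 4 agree to three decimals (0.65 and 0.75 need the non-integer x = 45.5 and 52.5). The table's arithmetic is sound.

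**2. Two denominators.** Assumptions: 70 starters, a fraction d lost before year 3 (the article gives no rate), and every lost patient a non-responder. The evaluable-only rate is x/[70(1 − d)], the all-starter rate is x/70, and their ratio is 1/(1 − d): 1.05, 1.11, 1.25 and 1.43 at d = 5%, 10%, 20% and 30%. Counts are rounded to whole patients.

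| Response among retained | Lost | Evaluable only (lower limit) | All starters (lower limit) |
|---|---|---|---|
| about 0.60 | 5% | 40/66 = 0.606 (0.478) | 40/70 = 0.571 (0.447) |
| about 0.60 | 10% | 38/63 = 0.603 (0.472) | 38/70 = 0.543 (0.419) |
| about 0.60 | 20% | 34/56 = 0.607 (0.468) | 34/70 = 0.486 (0.364) |
| about 0.70 | 10% | 44/63 = 0.698 (0.570) | 44/70 = 0.629 (0.505) |
| about 0.70 | 20% | 39/56 = 0.696 (0.559) | 39/70 = 0.557 (0.433) |
| about 0.80 | 20% | 45/56 = 0.804 (0.676) | 45/70 = 0.643 (0.519) |

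**3. Direction of the bias.** If excluded patients respond at rate q, the all-starter rate is (1 − d) × 0.60 + d × q. At d = 20%:
- q = 0: 0.48 + 0 = 0.48
- q = 0.30: 0.48 + 0.06 = 0.54
- q = 0.60: 0.48 + 0.12 = 0.60
- q = 0.80: 0.48 + 0.16 = 0.64

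The evaluable-only rate is too high only when q is below the rate among those retained.

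**4. Planned size.** Table 4 applies n = 70 to treated patients enrolled, whereas the GTR population is a subset of them. Loss of precision alone matters less: at an observed 0.60 the lower limit is 0.452 with 50 evaluable patients and 0.443 with 45.

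**5. Reach of the wider efficacy set.** It keeps 12 months of evaluations after stopping. A year-3 value therefore falls inside it only for a patient who stopped at month 36 − 12 = 24 or later. Someone who stopped at month 30 could be counted, and someone who stopped in year 1 would have no year-3 value within it.

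**The case against.** The strongest reply is that the 3-year phrase says when GTR is measured, not who is measured. Statistical analyses uses it as a time point for comparing GTRs, and ability to do the endurance test is recorded at baseline, so a baseline-able population assessed at year 3 is coherent. This stands as a possible reading. It does not settle the matter, because a primary denominator that can be read two ways needs correcting.

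A reader might infer that early discontinuers go uncounted on either reading. The article does not support that. On the timing reading it is silent about them, and the efficacy set under Patient population keeps some of their data after stopping.

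A reader might also infer that any patient who cannot walk or climb stairs is excluded. The text speaks only of the functional tests, and FVC is listed among them, so this is unclear.

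A flat statement that the rate is inflated would go too far as well. No attrition rate is given, and a patient who loses walking ability can still respond through the pharmacodynamic and quality-of-life domains.

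Finally, 45% is a planning reference and not a decision rule, and 0.60 is the least favourable row of Table 4. The Background section reports 29 of 33 (87.9%) in the integrated data. Near such a rate, moderate losses would leave the limit above 45%. All of this limits the size of the problem, but it does not repair the wording.

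**Conclusion.** The point holds as a defect in how the population is stated. The natural reading of Effectiveness variables and Study size selects on post-baseline status, and neither section is aligned with the wider efficacy set under Patient population. Inflation is likely, on the condition that excluded patients respond less often than those retained.

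At the plan's lowest assumed response, an assumed 5% loss (4 of 70 patients), all counted as non-response, is enough to take the lower limit below 45%. At 0.70, 10% loss does not do so but 20% does. These loss rates and the zero response among the lost are assumptions, so the figures illustrate sensitivity and do not estimate bias. With no formal test planned, crossing 45% changes how the result is described, not a decision. Should be fixed.

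**What to change.** Define the GTR population at treatment start: velmanase alfa-naïve, able to perform at least one Table 3 functional test at baseline, and started at least 3 years before the data cut. In the main analysis:
- count death, and discontinuation for lack of effect or an adverse event, as non-response;
- score a patient who loses the ability to do a test as not improved on that endpoint, and let the other endpoints and domains count as usual.

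This is milder than the illustration, which treats every loss as non-response. Counting these events as non-response is one defensible choice, so the year-3 evaluable patients should be reported as a supportive analysis. Bring Patient population, Effectiveness variables and Study size into line, so that the 70 in Table 4 refers to the same patients as the GTR denominator.

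The cost is protocol and SAP wording. Ability to do the endurance test and reasons for withdrawal are already collected. The reported GTR may be somewhat lower.
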